## Abstract

**Background:**

Australian farmers and their workers are exposed to a wide variety of pesticides. Organophosphate (OP) insecticides are a widely used class of pesticide used for animal husbandry practices (Naphthalophos for sheep dipping, jetting and drench), crop production for pest control (Dimethoate) and in public health (Maldison for head lice). Acute poisonings with this class of insecticide are reported among agricultural workers and children around the globe, due to the inhibition of acetylcholinesterase (AChE). Less is known about chronic exposures. Regular monitoring of erythrocyte AChE will enable farmers to identify potential exposure to organophosphate insecticides and take action to reduce exposures and improve their health and safety practices. This study aims to assess and improve the integration of AChE monitoring into routine point of care health clinics, and provide farming and non-farming people with a link between their AChE activity and their household chemical and agrichemical use.

**Methods/Design:**

The research will target individuals who work on mixed farming enterprises and routinely using OPs (*n* = 50) and non-farmers (*n* = 30). Baseline data are collected regarding demographic, health conditions and behaviours, Kessler 10 (K10) scores, chemical use and personal protection. Baseline anthropometric measures include height, weight, hip and waist circumference, body fat analysis and, biochemical analysis of fasted total serum cholesterol, triglycerides, low-density cholesterol (LDL), high-density cholesterol (HDL) and blood glucose. Analysis of erythrocyte cholinesterase (EAChE) activity is also conducted using a finger prick test. Testing of EAChE is then repeated in all participants every 3 weeks for a maximum of three times over a period 10 weeks. Participants are provided with full feedback and counselling about their EAChE activity after each reading and a detailed summary provided to all participants at the completion of the study. Data will be analysed using repeated measures within a general linear model.

**Discussion:**

This work will provide an evidence base and recommendations for the integration of EAChE monitoring into Australian rural health clinics, leading to research which will further quantify pesticide exposure both on the farm and in the home, highlighting the importance of sustaining and providing a safe work and home environment for farming communities.

**Trial registration:**

ACTRN12613001256763

## Background

Australian farmers and their workers are exposed to a wide variety of pesticides [1]. Pesticides are substances that destroy, repel or attack pests that have a negative effect on productivity and profitability of a farming enterprise. Pesticide groups include herbicides, insecticides, fungicides and rodenticides. Organophosphate (OP) insecticides are widely used for animal husbandry practices (Naphthalophos sheep drench), public health (head lice, locust control), and in crop production (Dimethoate for insect control). The OP class of insecticides effect the nervous system with poisonings most common among agricultural workers and children [2, 3]. OPs are regularly used as a form of pest control on most farms and farmers have enhanced their understanding of pesticide use and handling. However, many are still not meeting the full range of personal protection standards in their own handling and application [4]. Routes of human exposure include dermal absorption, inhalation and ingestion [5]. Symptoms of OP toxicity are caused by inhibition of the enzyme acetylcholinesterase (AChE). Inhibition of AChE results in the subsequent accumulation of acetylcholine at the cholinergic synapses of nerves causing uncontrolled firing of the synapse [1, 6]. Subclinical effects of chronic OP exposure such as AChE inhibition may be detected early by biological tests. Recovery from AChE depression is prolonged, due to the irreversible binding of OPs to the red blood cell and its subsequent 120 day life cycle [7]. Monitoring exposure to organophosphates involves the measurement of peripheral cholinesterase enzymes that are inhibited by organophosphates. These include; erythrocyte cholinesterase (EAChE) and serum cholinesterase (SAChE). Organophosphates have been associated with chronic neurological disease such as impaired memory, impaired fine motor skills control and Parkinson’s disease [8]. The evidence suggests that whilst an acute episode experience may not have occurred, exposure over a long period of time (such as in workers dipping sheep) may result in neurological conditions such as Parkinson’s disease and neuropsychiatric conditions [6, 8, 9]. The window for exposure to toxicants may occur years before the onset of neurological symptoms [8, 10, 11], this is particularly important for sheep and crop producers exposed to long-term, low levels of OPs. The Western region of the state of Victoria in Australia has been a centre of sheep production, since settlement, and a large number of farmers have been exposed to OPs through routine sheep dipping (lice control), drenching (control internal parasites), jetting (blow fly control) and spraying of pastures (insect control). The National Centre for Farmer Health (NCFH) is in a unique position to monitor these farmers and workers, and work with farmers to incorporate cholinesterase testing as part of their assessments during peak periods and provide much needed data for them on exposures in this area. Additional practices such as mixing contaminated laundry and storing pesticides in the home are not only common causes of exposure to the farmer and farm worker, but may also be placing other household members at risk, particularly children [12]. Work completed by the program Sustainable Farm Families™ [13] has identified that there is strong interest from farm men and women who wish to investigate exposures and possible health impacts of agricultural chemical use.

The acute effect of OP exposure is well documented in Australia and overseas for humans, pests and animals [3, 6, 9]. However, the extent to which asymptomatic monitoring is taking place is not well known or documented. This research builds on work conducted by the NCFH. It utilises the data collection methods of the Sustainable Farm Families™ which includes health behaviours and conditions, with the expectation that this monitoring EAChE testing will be integrated into this procedure, providing the springboard to break through barriers that are currently inhibiting best practice chemical handling safety in Australia.

Understanding the mode of action of a chemical is a critical component of the risk assessment process. Cholinesterase activity is a direct link to exposure and this pilot study will produce valuable data on possible exposures for farmers routinely using OP’s for animal husbandry or crop production.

Monitoring cholinesterase levels during agricultural health screening and assessment is a key objective of Agrisafe™ clinics in Australia. However, its incorporation into such clinics will depend on health professional’s skills and knowledge. This study will further prepare health care providers for integration of correct cholinesterase testing procedures into point of care (POC) health checks. This work will further highlight pesticide exposure as a risk for farmers, workers and their families, leading to an easily adopted method that will quantify the environmental exposures providing early detection. Research has also shown links between cholinesterase activity and vascular complications in diabetic patients [14]. Diabetes is a disease also of increasing concern to the farming and rural population in Australia [15].

### Aims

The Cholinesterase Research Outreach Project (CROP) will use clinical sampling to determine the level of exposure associated with the routine use of OPs by Victorian farmers and/or their workers. This preliminary study will examine the methodology of testing for EAChE activity at POC and provide evidence for future work by identifying the exposure patterns and pathways of individuals most at risk in farming communities. It is anticipated that CROP will inform future research studying pesticide exposure in farming communities.

## Methods/design

### Evaluation design

To evaluate if a difference in cholinesterase activity was present in farmers before and after exposure, sample size is determined at the power of 80 % (β = 0.2) with α set at 0.05 for an effect size of one standard deviation. This requires the sample size to be a minimum of 30 farming individuals exposed to pesticides. By considering the probable retention rate (≥85 %) for a 7-month study, based on previous research in similar populations, [16] the target recruitment number is fixed at a target of 50 farmers.

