### Data entry, handling and statistical analysis

All data will be managed and analysed within the statistical program SPSS (IBM Corp. Released 2012 IBM SPSS Statistics for Windows, Version 21.0. Armonk, NY). SPSS is a statistical package widely used in quantitative social science research and is suitable for multivariate analysis. Data will be analysed using repeated measures (subjects as own controls) within the General Linear Model. Correlation coefficients between pesticide exposure and metabolic variables will be calculated using Pearson’s and Spearman’s correlation as appropriate. P values will be considered statistically significant at *p* < 0.05.

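### The stated inputs yield neither the minimum of 30 farmers nor the target of 50; the error is conservative, but the stated sensitivity is wrong

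*Protocol article*

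**What the plan says.** The calculation is in the protocol article, Methods/design, Evaluation design. The question is a comparison within farmers: "To evaluate if a difference in cholinesterase activity was present in farmers before and after exposure". Power is set at 80%, "with α set at 0.05 for an effect size of one standard deviation". The stated result is: "This requires the sample size to be a minimum of 30 farming individuals exposed to pesticides". The section then refers to a probable retention rate of at least 85% over a seven-month study, after which "the target recruitment number is fixed at a target of 50 farmers".

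The section on data entry, handling and statistical analysis confirms that the comparison is within person: "Data will be analysed using repeated measures (subjects as own controls) within the General Linear Model".

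The article does not say whether the one SD is that of the within-farmer change or the spread between people. It gives no sidedness for the calculation and no correlation between readings. A full protocol may hold these details, and their absence is not the point here. The point is that the published inputs and the published results do not agree.

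**The concern.** This is the only planning calculation in the article, and it has two links: from the inputs to 30, and from 30 to 50. A one-SD shift is a large effect for a design in which each person is their own control, so 30 looks too many. An allowance for at most 15% loss cannot plausibly add 20 people to 30.

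At stake is how the study's sensitivity is described. A reader is told that one SD is the effect for which the study is sized, when the planned number can detect a clearly smaller change. The Aims section says the project should inform later research, so a later team that reused this calculation would carry the error forward.

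**Working it through.** **Inputs from the article.** Paired before/after comparison in farmers; power 80%; alpha 0.05; effect 1 SD; stated minimum 30; retention at least 85%; stated target 50.

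**Assumptions added here.** Two-sided test. The SD is read in two ways: (a) the SD of the within-farmer change; (b) the between-person SD, with correlation ρ between readings. The article gives no ρ, so a range is shown.

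**Step 1: from the inputs to 30.**

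Normal approximation, reading (a): n = ((1.960 + 0.842)/1)² = 7.85, so 8.

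Exact paired t-test, reading (a): the noncentrality is d√n with n − 1 degrees of freedom. For d = 1, n = 9 gives 74.8% power and n = 10 gives 80.3%. The requirement is **10**. A one-sided test needs 8.

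Reading (b): the SD of the change is √(2(1 − ρ)) between-person SDs, so d = 1/√(2(1 − ρ)).

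| ρ | d | n (two-sided, exact t) |
|---|---|---|
| 0 | 0.707 | 18 |
| 0.25 | 0.816 | 14 |
| 0.5 | 1.000 | 10 |
| 0.7 | 1.291 | 7 |
| 0.9 | 2.236 | 4 |

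The stated 30 is not reproduced. Under (b) it would take a correlation of about −0.79 between two readings in the same person.

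For comparison, two independent groups would need 16 per group by the normal formula (32 in total) or 17 per group by exact t (34 in total). The total is close to 30, but the design is not the one stated, and the stated 30 are all farmers measured before and after.

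**Step 2: from 30 to 50.**

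30/0.85 = 35.3, so **36**. Retention is given as at least 85%, so 36 is the most that this allowance can require. Working back, 30/50 = 0.60, so a target of 50 corresponds to 60% retention. Applying 85% at each of three visits gives 0.85³ = 0.614 and 30/0.614 = 48.8, so 49, but the article states the rate for the whole study. This step does not depend on the SD, the correlation or the sidedness.

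**Step 3: what the planned number can detect.**

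Completers: 50 × 0.85 = 42.5, taken as 42. Solving the exact paired t-test for 80% power at two-sided 0.05 gives 0.53 SD of the change at n = 30 and 0.44 at n = 42. Power for one SD of the change at n = 30 is 99.96%.

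Under reading (b), with n = 42, the detectable change in between-person SDs is 0.443 × √(2(1 − ρ)):

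| ρ | Detectable change (between-person SD) |
|---|---|
| 0 | 0.63 |
| 0.25 | 0.54 |
| 0.5 | 0.44 |
| 0.7 | 0.34 |

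**The case against.** **The error is on the safe side.** More farmers are recruited than the inputs need, power is not short, and no analysis or decision rule changes. The article calls the work a pilot and a preliminary study. This stands, and it limits the severity.

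**Thirty can be approached.** Table 1 schedules four erythrocyte cholinesterase readings, and the analysis is a repeated-measures model. Take a four-visit within-subject F test with a range of one between-person SD between the extreme visits, the other two midway, and zero correlation. It needs 24 farmers under sphericity and 29 with a sphericity correction of 0.75. A paired test with Bonferroni adjustment over six visit pairs at zero correlation needs 28. So a reader should not infer that no reading comes near 30. These routes rest on pessimistic assumptions that the article does not state, and at a correlation of 0.5 the F-test figures fall to 13 and 15. They do not rescue the text.

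**Minimum and target leave room for rounding up.** A target of 50 does satisfy a need for 36, and the article never writes out the division. But it presents 30 as what the inputs require, and it gives retention as the only reason for 50.

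**Two stronger readings go too far.** A reader might infer that the study always detects effects less than half the stated size. That holds at 42 completers on the change-SD reading, but not for a between-person SD at low correlation (0.63 at ρ = 0, 0.54 at ρ = 0.25). A reader might also infer that the article misinterprets a null result. It says nothing about how a null result will be read, and that would rest on the confidence interval from the data rather than on the planning effect.

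**Conclusion.** Wrong as written, in the conservative direction, and so not a defect that must be fixed before the study can proceed. The stated inputs give 10 farmers if the SD is that of the within-farmer change, and about 4 to 18 if it is the between-person SD with correlation from 0.9 to 0; they do not give 30. These figures assume a two-sided paired t-test, and a one-sided test does not raise them. Retention of at least 85% takes 30 to 36 at most, not 50, whatever is assumed about the SD.

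The study is not underpowered. Its stated sensitivity is wrong on both readings of the SD. The exact detectable change depends on an SD definition and a correlation that the article does not give, so it can only be stated as a range.

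**What to change.** Keep 50 farmers and rewrite the paragraph in Evaluation design:

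- Delete the statements that a one-SD effect requires 30 farmers and that 85% retention leads to 50. Alternatively, describe 50 as set on other grounds and state them.
- Say which SD is meant. The authors must settle this, because the document does not, and no definition should be imposed on them.
- State the detectable change for about 42 completers (50 × 0.85), with 80% power and two-sided alpha 0.05. If the SD is that of the within-farmer change, this is 0.44 SD. If it is the between-person SD, give the assumed correlation and the matching figure: about 0.63, 0.54, 0.44 or 0.34 SD at correlations of 0, 0.25, 0.5 or 0.7.

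The cost is one rewritten paragraph. No participants, visits or analyses are added.

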### Sample size and inclusions

Consent will be obtained from 80 participants recruited via existing contacts and industry groups, letterbox drops and newspaper articles from a number of farming and community groups, specifically;

Mixed farming enterprises and sheep dipping/spraying contractors (*n* = 50) who are using OPs and a convenience group of non-farming individuals (*n* = 30) from the rural community of Hamilton, Australia.

Participants need to have been farming for more than 5 years, be aged between 18 and 75 years, speak English, and not had a previous known chemical incident. Questionnaires will be used to determine whether or not they are the primary pesticide user. Any non-farming individuals tested must also be aged between 18 and 75 and have not had a previous chemical incident. Participants from both groups will be self-reported not pregnant, not suffering from a known chronic disorder, not taking anti-inflammatory drugs or supplements and not exercising excessively throughout the study.

### Anthropometry

The simplicity of anthropometry allows it to be used in population-based studies to assess body-composition changes over time, as well as in clinical and field situations where access to technology is limited such as in this study. Height, weight, waist and hip circumference has previously been included as part of an initial POC assessment for farm men and women and agricultural workers. Participants have found these measurements helpful and easy to understand and also cite having a free health assessment as a reason to attend [13]. Additionally, (whilst not the focus of this study) if used in combination with blood biochemistry and body fat percentage, anthropometry can identify distinct fat distribution changes that occur in the elderly [17]. Weight is measured to the nearest 0.05 kg using electronic scales taken in light clothing with shoes removed and pockets emptied and prior to breakfast. Height is measured using a portable stadiometer to the nearest 0.1 cm with shoes removed and weight distribute evenly on both feet.

### Physical assessments and health condition data

A short health history and health behaviours (smoking and alcohol consumption habits) will be obtained from participants with baseline physical assessments of blood pressure measurement (repeated twice), pulse rate, body fat percentage (bioelectrical impedance), respiratory function test (PiKo meter) also measured (see Table 1). Biochemical analysis of EAChE activity using a 10 μl capillary blood sample (measured by Test-mate ChE Cholinesterase tester system Model 400), and EAChE field Assay kit - to establish a baseline reading, will be used (Fig. 1). The Test-mate field assay testing system is based on the Ellman method [18]. Blood glucose and lipids (LDL, HDL) and total cholesterol is also taken after 10-hour fast using the same blood sample.

**Table 1 Tab1:** Data collection description and timeline for farmer and non-farmer groups

Variable	Baseline (T0)	Visit 1 (T1, 1 mth)	Visit 2 (T2, 2 mth)	Visit 3 (T3, 3 mth)
Body weight	✓	X	X	X
Height	✓	X	X	X
Waist circumference	✓	X	X	X
Hip circumference	✓	X	X	X
Body fat %	✓	X	X	X
Blood pressure	✓	X	X	X
Pulse rate	✓	X	X	X
Fasting blood glucose	✓	X	X	X
Fasting blood cholesterol	✓	X	X	X
Fasting triglycerides	✓	X	X	X
HDL cholesterol	✓	X	X	X
LDL cholesterol	✓	X	X	X
Erythrocyte Cholinesterase (EAChE)	✓	✓	✓	✓
Description of monthly chemical use	✓	✓	✓	✓
Kessler (K10)	✓	X	X	X
Chemical Usage Survey	✓	X	X	X

**Fig. 1 Fig1:**
[figure not shown]
Point of care schedule for cholinesterase assessment

Waist circumference is measured to the nearest 0.1 cm at the end of a normal expiration using a constant tension “Figure Finder Tape Measure”™ [19]. Body Mass Index will be calculated to classify obesity and overweight cut off points for future reference using the WHO parameters [20].

### Survey methodology

Trained research staff will collect all anthropometric and behavioural data. Sociodemographic data are collected directly from the participant including age, gender, country of origin, using the Victorian Department of Health service coordination tools (SCOT) [21]. The type of farming undertaken and residential postcode will also be collected from the participants.

A validated questionnaire, the Kessler 10 (K10) will be used to measure psychological distress. The K10 is a 10-item questionnaire intended to yield a global measure of distress based on questions about anxiety and depressive symptoms that a person has experienced in the most recent 4 week period [22]. This survey has been used extensively in Australia and provides a comparison to the general population. Given the relationship between organophosphates, neuropsychological and psychiatric functioning a baseline was deemed important [23, 24]. It also forms part of the usual farmer health assessment.

### Occurrence of illness & injury

Occurrence of illness or injury experienced within the last 3 months will be measured using a questionnaire describing 33 symptoms of chemical exposure, in random order of severity. The illness and injury data will be standardised and analysed accordingly.

### Monitoring agrichemical use

In addition to completion of the agrichemical use survey of 13 questions, self-reported chemical use is recorded during each visit. Participants are provided with counselling regarding their EAChE levels in accordance with AgriSafe guidelines (Fig. 2). The USA’s Department of Pesticide Regulation specifies that a drop to 70 % or lower in red blood cell AChE or to 60 % or lower in plasma cholinesterase relative to the individual’s baseline is an indication for immediate removal of the individual from all exposure to organophosphate and carbamate pesticides [25]. Participants will be provided with a summary of their EAChE baseline and subsequent results at the conclusion of the study. This methodology reflects recent exposures and is used to provide feedback at the time of testing. However, it is noted that the level of current exposure is not a measure of long-term exposure and that the clinical parameters around long-term exposure are not well defined.

**Fig. 2 Fig2:**
[figure not shown]
Guide to severity of acute poisoning with anti-cholinesterase agents (Source: Modified from California Environmental Protection Agency 2002)

### Data entry, handling and statistical analysis

All data will be managed and analysed within the statistical program SPSS (IBM Corp. Released 2012 IBM SPSS Statistics for Windows, Version 21.0. Armonk, NY). SPSS is a statistical package widely used in quantitative social science research and is suitable for multivariate analysis. Data will be analysed using repeated measures (subjects as own controls) within the General Linear Model. Correlation coefficients between pesticide exposure and metabolic variables will be calculated using Pearson’s and Spearman’s correlation as appropriate. P values will be considered statistically significant at *p* < 0.05.

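### Repeated-measures GLM in SPSS uses only farmers with all four EAChE readings; a mixed model on all available readings would avoid discarding partial series and possible selection bias

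*Protocol article*

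**What the plan says.** Under Data entry, handling and statistical analysis, the Protocol article names the software ("All data will be managed and analysed within the statistical program SPSS", version 21) and the model: "Data will be analysed using repeated measures (subjects as own controls) within the General Linear Model". The abstract names the same model. No method that keeps participants with partial series is mentioned.

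Table 1 schedules an EAChE reading at baseline and at each of three follow-up visits, in both groups. The abstract describes the schedule this way: "Testing of EAChE is then repeated in all participants every 3 weeks for a maximum of three times over a period 10 weeks".

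Under Evaluation design, the comparison of interest is EAChE in farmers before and after exposure, and "sample size is determined at the power of 80 % (β = 0.2) with α set at 0.05" "for an effect size of one standard deviation". The minimum is 30 farmers. Loss enters only there: "By considering the probable retention rate (≥85 %) for a 7-month study", the recruitment target is set at 50.

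The abstract and the section on monitoring agrichemical use both say that participants are counselled on their EAChE results as the study proceeds; the abstract says this happens after each reading.

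**The concern.** The standard SPSS repeated-measures GLM takes one column per visit and leaves out any participant with an empty cell. The protocol does not state this rule; it comes with the procedure it names. A farmer with T0, T1 and T2 but no T3 would contribute nothing, not even to the T0-to-T1 change.

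Two things are at stake. Readings already collected are thrown away. And those who remain may be a selected group: a farmer told that activity has fallen may be less likely to come back, or more likely. The retention allowance protects the number of completers but not their representativeness. The study sets out to measure how far EAChE moves with routine OP use, so selection on that movement would affect its main result.

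**Working it through.** **Inputs from the protocol.** 50 farmers and 30 non-farmers; four readings (Table 1); retention of at least 85%; power 80%, alpha 0.05 (two-sided assumed), effect 1 SD.

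**The plan's own figures.** A paired comparison needs n = ((1.96 + 0.84)/1)² = 7.84, so 8, or 10 with the t distribution. Allowing for 15% loss, 30/0.85 = 35.3, so 36. Neither the 30 nor the 50 is reproduced. That is a separate matter, and 50 is taken as given here.

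**Complete series.** With 15% overall loss, 50 × 0.85 = 42.5, so about 42 farmers (80 × 0.85 = 68 overall). If, in addition, each of the three follow-up readings is missed independently with probability m (an assumption), the count is 50 × 0.85 × (1 − m)³:

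- m = 2%: 40.0
- m = 5%: 36.4

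**Power.** By the noncentral t, power for a 1 SD paired change is above 99.9% with 42 completers. It is still 99.8% with 26, which is the count at m = 15% (50 × 0.85 × 0.85³ = 26.1). The stated test is not at risk.

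**Bias.** This scenario is assumed; the documents give no mechanism. There are four readings with SD 1 and equal correlation of 0.6 or 0.8. The true change is -0.50 SD at T1, T2 and T3. 15% are lost after T1, with 200,000 simulated participants per cell so that chance error is negligible. Completers are compared with a likelihood estimate that uses every reading.

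| Loss after T1 | Correlation | Completers T1 | Completers T3 | All readings T3 |
|---|---|---|---|---|
| Random | 0.6 | -0.500 | -0.500 | -0.499 |
| Random | 0.8 | -0.501 | -0.499 | -0.499 |
| Odds double per SD of larger fall | 0.6 | -0.417 | -0.456 | -0.500 |
| Odds double per SD of larger fall | 0.8 | -0.437 | -0.469 | -0.500 |
| Odds triple per SD of larger fall | 0.6 | -0.374 | -0.435 | -0.497 |
| Odds triple per SD of larger fall | 0.8 | -0.411 | -0.454 | -0.499 |
| The 15% with largest falls leave | 0.6 | -0.257 | -0.378 | -0.500 |
| The 15% with largest falls leave | 0.8 | -0.327 | -0.413 | -0.500 |

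The shortfall at T3 is 1 − 0.469/0.5 = 6% to 1 − 0.456/0.5 = 9% when the odds double, 9% to 13% when they triple, and 17% to 24% in the extreme case. At T1 it is larger: 13% to 17% when the odds double (1 − 0.437/0.5, 1 − 0.417/0.5).

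**Direction.** The scenario is symmetric. If a larger fall makes a farmer more likely to return, the error has the same size and the opposite sign. With doubled odds, completers would give -0.53 to -0.54 at T3 (-0.50 − 0.031, -0.50 − 0.044).

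**The case against.** The strongest reply is that the protocol states no deletion rule, and that handling of missing data may stand in an analysis plan that is not shown. That holds as far as it goes: the absence of a missing-data section is no fault. But the article does fix the model and the software, and the point is about that choice.

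A reader might infer more than the documents support:

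- *That only about 31 of 50 farmers would be complete.* This comes from applying 15% independently to each reading (50 × 0.85³ = 30.7). The protocol's figure is retention of participants over the study, which leaves about 42.
- *That unequal series are planned.* The abstract's "for a maximum of three times over a period 10 weeks" can be read as a cap, and Table 1 schedules all three follow-ups for everyone.
- *That 15% loss is to be expected.* The retention figure is a minimum, quoted for 7 months. Testing runs 10 weeks in the abstract or 3 months in Table 1, so loss may be smaller.
- *That the result will be biased, or too small by about a quarter.* No section says that attendance depends on results. Random loss gives no bias, a shortfall near a quarter at T3 needs the extreme row of the table, and the sign is unknown.

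The study also calls itself preliminary, and power for its stated effect is ample. These points limit the size of the problem. They give no reason to prefer a procedure that discards partial series.

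**Conclusion.** The point holds in a limited form. The named procedure, run in the standard way, analyses only participants with all four EAChE readings. At the loss the plan allows, that is about 42 of 50 farmers, or fewer if other single visits are missed. The remaining farmers' readings would go unused. The estimated change could be biased either way if attendance depends on earlier readings, which feedback after each test makes plausible but does not establish. Under the assumed scenario with moderate dependence (odds of loss two to three times per SD), the error at T3 is roughly 6% to 13% of the true change; under random loss it is nil. Power for the 1 SD effect is unaffected in practice.

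These sizes rest on assumed correlations, a single time of loss, and loss that depends only on the observed T1 change. The last assumption favours the likelihood estimate by construction. This is an inexpensive improvement to a stated method, not a defect that would invalidate the study.

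**What to change.** Replace the GLM sentence with a likelihood-based linear mixed model for repeated measures (SPSS MIXED, REML) on all available T0 to T3 readings:

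- visit as a categorical factor;
- group and group-by-visit terms where farmers and non-farmers are compared;
- an unstructured within-participant covariance, with a simpler structure named in advance in case it does not converge;
- the complete-case GLM kept as a sensitivity analysis.

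Visit should be a factor, not linear time in days. For the course assumed above (0, -0.5, -0.5, -0.5) with no missing data, a straight line has slope (−1.5×0 − 0.5×(−0.5) + 0.5×(−0.5) + 1.5×(−0.5))/5 = −0.15 per visit. It would report -0.15 at T1 and -0.45 at T3, against a true -0.5 at both. A dip with partial recovery would be fitted poorly for the same reason.

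The cost is a few sentences and slightly more modelling work, with the same data and software. Each participant still serves as their own control. The new analysis relies on missingness being explained by the readings already observed; if attendance depends on unrecorded exposure or on the unseen reading itself, it can be biased too.
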